**10.5.3　Secondary Outcome Analysis**

(1) Operative time

(2) Estimated blood loss

For FAS, calculate summary statistics (sample size, mean, standard deviation, minimum, median, maximum) by group. Perform Student's t-test for between-group comparisons and calculate p-values.

(3) Proportion achieving the minimal clinically important difference (MCID) in cervical JOA score recovery rate at postoperative 1 and 2 years

For the FAS, calculate the proportion achieving the MCID (JOA score recovery rate of 52.8%) for the cervical JOA score recovery rate at postoperative 1 year and 2 years by group. For between-group comparisons, calculate the difference in the proportion achieving the MCID (52.8% recovery rate) and its 95% confidence interval, then perform Fisher's exact test. Use the Clopper-Pearson method to calculate the confidence interval.

(4) Health-related QOL (EQ-5D) at postoperative 1 and 2 years

(5) Severity of neck pain, upper limb pain, and upper limb numbness (VAS) at postoperative 1 and 2 years

(6) Neck disability index (NDI) at postoperative 1 and 2 years compared to preoperative

For FAS, perform analyses similar to those for primary endpoints on the change in each assessment item from preoperative to 1 year postoperatively.

Additionally, perform analyses similar to those for secondary endpoint (2) on the change in each assessment item from preoperative to 1 year and 2 years postoperatively.

(7) Retention rate of enlarged lamina at postoperative 1 and 2 years (Retention rate)

For FAS, the change in the retention rate of enlarged lamina from preoperatively to 1 year postoperatively will be analyzed similarly to the primary endpoint.

Furthermore, the change in the retention rate of enlarged lamina from preoperatively to 1 and 2 years postoperatively will be analyzed similarly to secondary endpoint (2).

(8) Percentage of hinge fractures at postoperative 1 and 2 years

(9) Percentage of bone union of gutter at postoperative 1 and 2 years

For FAS, calculate the percentage for each evaluation item at 1 year and 2 years postoperatively by group. For between-group comparisons, calculate the difference in the percentage for each evaluation item and its 95% confidence interval, and perform Fisher's exact test. Use the Clopper-Pearson method to calculate the confidence interval.

　(10) Sagittal alignment of cervical spine at postoperative 1 and 2 years (C-SVA, C2-7 angle, T1 slope)

For FAS subjects, perform analyses similar to those for primary endpoints on the change in each evaluation item from preoperatively to 1 year postoperatively.

Additionally, perform analyses similar to those for secondary endpoint (2) on the change in each evaluation item from preoperatively to 1 and 2 years postoperatively.

(11) Paraspinal muscle cross-sectional area (C4/5 level) at postoperative 1 and 2 years

For FAS, perform the same analysis as for primary endpoints on the change in paraspinal muscle cross-sectional area from preoperatively to 1 year postoperatively.

Additionally, perform the same analysis as for secondary endpoint (2) on the change in paraspinal muscle cross-sectional area from preoperatively to 1 and 2 years postoperatively.

(12) Dural sac cross-sectional area (C3/4, C4/5, C5/6, C6/7 levels) at postoperative 1 and 2 years

For FAS subjects, perform the same analysis as for the primary endpoint on the change in dural canal area from preoperative to 1-year and 2-year postoperative time points.

Additionally, perform the same analysis as for secondary endpoint (2) on the change in dural canal area from preoperative to 1-year and 2-year postoperative time points.

(13) Grading of the mass posterior to the dural sac at postoperative 1 and 2 years

For FAS subjects, classify posterior spinal canal compression at 1 and 2 years postoperatively into mild (Grade 1-3) and severe (Grade 4-5). Calculate the proportion of severe posterior spinal canal compression at 1 and 2 years postoperatively by group. For between-group comparisons, calculate the difference in the proportion for each evaluation item and its 95% confidence interval, then perform Fisher's exact test. Use the Clopper-Pearson method to calculate the confidence interval.

(14) Incremental Cost-Effectiveness Ratio (ICER)

Calculate the ICER of the test treatment group relative to the control group.

Refer to Section 8.1.2 for details on the calculation method.

(15) Surgical complication incidence

For SAS, calculate the number of cases and rates of each complication by the following categories for each assigned group.

・Intraoperative complication rate (from start of surgery to end of surgery (wound closure))

・Early postoperative complication rate (from end of surgery (wound closure) to within 30 days postoperatively)

・Late postoperative complication rate (from postoperative day 31 to within 2 years postoperatively)

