**＜Secondary Endpoints＞**

(1) Operative Time

(2) Estimated Blood loss

[Definition]

Operating time is defined as the time recorded in the anesthesia record.

Blood loss is defined as the amount recorded in the anesthesia log. If “minor bleeding” is recorded, it is considered 10 ml of blood loss.

(3) Proportion achieving the MCID in cervical JOA score recovery rate at postoperative 1 and 2 years

[Definition]

Refer to the description under <Primary Evaluation Items> for the definition of JOA score recovery rate.

Following previous reports19), the MCID for JOA score recovery rate is set at 52.8%. The MCID achievement rate at 1 year and 2 years postoperatively is evaluated for each group.

(4)　 Health-related QOL (EQ-5D) at postoperative 1 and 2 years

[Definition]

Obtained via patient self-completion of the Japanese-language questionnaire (attached separately). If the patient cannot complete the questionnaire due to writing difficulties caused by cervical myelopathy, family members or healthcare professionals will assist with completion.

Health-related QOL will be assessed using the EQ-5D before surgery, postoperative 1 year, and 2 years. Note: The EQ-5D is also used as the utility value when calculating the incremental cost-effectiveness ratio (11).

(5) Severity of neck pain, upper limb pain, and upper limb numbness (VAS) at postoperative 1 and 2 years

[Definition]

Obtained through the patient's own completion of a questionnaire form created in Japanese (attached separately). If the patient cannot complete the questionnaire due to writing difficulties caused by cervical myelopathy, a family member or healthcare professional will assist with completion.

The severity of pain and numbness will be assessed using a 0–100 mm VAS before surgery and at postoperative 1 and 2 years.

(6) Neck disability index (NDI) at postoperative 1 and 2 years compared to preoperative

[Definition]

Data is collected via the Japanese version questionnaire (attached separately) completed by the patient themselves. If the patient cannot complete the questionnaire due to writing difficulties caused by cervical myelopathy, family members or healthcare professionals will assist with completion.

Health-related QOL due to cervical spine disease is assessed before surgery, and postoperative 1 year and 2 years using the NDI total score.

[figure not shown]
(7) Retention rate of enlarged lamina at postoperative 1 and 2 years (Retention rate)

[Definition]

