**10.2　Target Enrollment Numbers and Rationale**

Target enrollment: 216 cases

(Control group [mini-plate]: 108 cases, Test treatment group [suture-anchor]: 108 cases)

[Rationale]

Regarding the primary endpoint, the recovery rate in cervical JOA scores before and after surgery, a retrospective pilot study at Saiseikai Kawaguchi General Hospital, which used a patient population similar to this study, reported rates of 49.9±22.8% (21 cases) for the plate method and 52.6±32.9% (20 cases) for the suture anchor method (unpublished data).

Furthermore, a previous report^3)^ indicated that the MCID for compressive myelopathy is 52.8%. Based on the pilot study and past MCID findings, the recovery rate in cervical JOA scores for the control group (plate method) in this study was set at 50% (standard deviation 40%), with a non-inferiority margin of 20%. With a significance level (one-sided) of 0.025 and

and a power of 0.9, the required sample size for both groups combined is 172 cases. Anticipating approximately 20% dropout, the target sample size for both groups combined was set at 216 patients.

This target enrollment number is treated as an anticipated enrollment number, and exceeding this anticipated number is permitted. However, the Principal Investigator (PI) shall manage the cumulative actual enrollment numbers across all participating institutions to ensure the total number of cases does not exceed the study's target enrollment. If additional enrollment is required to meet the overall study target, prior approval must be obtained from the Ethics Review Committee or equivalent body.

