**10.5.2　Analysis of Primary Endpoints**

・Recovery Rate in Cervical JOA Score Before and After Surgery

For FAS participants, calculate the least squares mean and its 95% confidence interval for the cervical JOA score recovery rate at 1 year post-surgery using analysis of covariance. Also calculate the between-group difference in least squares means (suture anchor method vs. plate method), its 95% confidence interval, and the p-value. The analysis model included the following covariates: group, preoperative JOA score, age (≤64 years, 65–74 years, ≥75 years), sex, and preoperative diagnosis (cervical spondylotic myelopathy (CSM), ossification of the posterior longitudinal ligament (OPLL)).

The suture-anchor method will be considered non-inferior to the mini-plate method if the lower limit of the 95% confidence interval for the least squares mean difference between groups at 1 year postoperatively exceeds –20%. Additionally, as a secondary analysis, a Mixed-effects Model for Repeated Measures (MMRM) analysis will be performed using the first available subject (FAS) population, with the recovery rate in cervical JOA scores at 1 year and 2 years postoperatively relative to preoperatively as the response variable. The analysis model will include the following as fixed effects: group, time point, group-time interaction, preoperative JOA score, age (≤64 years, 65–74 years, ≥75 years), sex, and preoperative diagnosis (CSM, OPLL). Using this model, the least squares mean and 95% confidence interval for the recovery rate in cervical JOA scores before and after surgery at 1 year and 2 years postoperatively will be calculated. Additionally, the between-group differences in the recovery rate of cervical JOA scores before and after surgery at 1 year and 2 years postoperatively, along with their 95% confidence intervals and p-values, were calculated.

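### The MCID responder comparison (Protocol 10.5.3 item (3)) is valid but conservative: it uses Fisher's test without the primary covariates, and names a single-proportion interval for a difference

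*Protocol*

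**What the plan says.** Protocol 8.2 defines a responder through a threshold: "the MCID for JOA score recovery rate is set at 52.8"%. Section 10.5.3 item (3) compares responders between arms at 1 and 2 years. The analyst is to "calculate the difference in the proportion achieving the MCID (52.8% recovery rate) and its 95% confidence interval", run Fisher's exact test, and obtain the interval by Clopper-Pearson. No covariate is named.

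Section 10.5.2 treats the undivided recovery rate differently: "The analysis model included the following covariates: group, preoperative JOA score, age" group, sex and preoperative diagnosis. The mixed model for 1 and 2 years in the same section carries the same covariates. Section 5.3 allocates by minimisation on facility, age, gender and diagnosis. It justifies the last three on prognostic grounds.

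Section 5.1, rationale (3), presents the responder proportion as a complement to the direct comparison of recovery rates. It is a secondary endpoint. No non-inferiority margin and no power target are set for it.

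**The concern.** The responder variable is the primary variable cut in two. Cutting already discards information, and item (3) then sets aside baseline variables that the protocol itself regards as prognostic and collects anyway. When allocation is balanced on prognostic factors, leaving them out gives a valid estimate but tends to make the test conservative. Fisher's test adds conservatism of its own.

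The direction matters here. The primary margin is 20 points, so the responder comparison is a natural place to see whether a non-inferior mean hides a loss of patients with worthwhile recovery. A conservative difference test misses such a loss more often.

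The interval is a separate fault. Clopper-Pearson bounds one binomial proportion. Applied to each arm it gives two intervals, not one for the difference that the sentence asks for. As written, the main estimate of item (3) has no defined interval.

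**Working it through.** **Inputs.** Section 10.2 gives the control arm: the recovery rate "was set at 50% (standard deviation 40%), with a non-inferiority margin of 20"%. It also gives "With a significance level (one-sided) of 0.025 and" "and a power of 0.9, the required sample size for both groups combined is 172 cases". Allocation is equal ("Control group [mini-plate]: 108 cases, Test treatment group [suture-anchor]: 108 cases"). The responder threshold is 52.8% (8.2). Three assumptions are not in the protocol: a true difference of 0 in the sample size calculation, normally distributed recovery rates, and the share of variance (R²) explained by the baseline factors, taken as 0 to 0.3.

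**The plan's own figure.** Normal approximation: n per arm = 2 × (1.960 + 1.282)² × 40² / 20² = 84.1, rounded up to 85, or 170 in total. With the t distribution, 86 per arm gives power 0.903, so 172 reproduces. Dropout: 172 / (1 − 0.20) = 215, or 216 in equal arms, which also reproduces. The checks below use 86 per arm.

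**Responder proportions.** P(recovery ≥ 52.8) = 1 − Φ((52.8 − mean)/40).
- Mean 50: 1 − Φ(0.07) = 47.2%.
- Mean 40 (10-point deficit): 1 − Φ(0.32) = 37.4%.
- Mean 34 (16-point deficit): 1 − Φ(0.47) = 31.9%.
- Mean 30 (20-point deficit): 1 − Φ(0.57) = 28.4%.

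**Size and power, two-sided 0.05, 86 per arm.** Fisher and Pearson are by exact enumeration of all tables. The adjusted column is by simulation, as a range over R² from 0 to 0.3.

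| Mean deficit | Responders | Fisher | Pearson | Adjusted |
| --- | --- | --- | --- | --- |
| 0 | 47.2 v 47.2% | 0.039 | 0.056 | about 0.05 to 0.06 |
| 10 | 47.2 v 37.4% | 0.22 | 0.27 | 0.27 to 0.32 |
| 16 | 47.2 v 31.9% | 0.481 | 0.544 | about 0.54 to 0.62 |
| 20 | 47.2 v 28.4% | 0.67 | 0.73 | 0.72 to 0.80 |

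**Splitting the loss at the 16-point deficit.** Fisher to unadjusted Pearson: 0.544 − 0.481 = 0.063, about 6 points, with no covariates involved. Pearson to adjusted: 0.54 − 0.54 = 0 up to 0.62 − 0.54 = 0.08, so about 0 to 8 points. If all 108 per arm were evaluable, Fisher's size would be 0.034 and its power 0.582 against 0.633 for Pearson, a gap of about 5 points.

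**Interval width at the 16-point deficit.** Unadjusted standard error: √(0.472 × 0.528/86 + 0.319 × 0.681/86) = 0.074; the simulated average was 7.3 points. With adjustment it was 7.2, 7.0 and 6.7 points at R² of 0.1, 0.2 and 0.3. Multiplying by 1.96, the half-width goes from 14.3 to 14.1, 13.7 and 13.1 points. The gain is 0.2 to 1.2 points.

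**The case against.** The strongest reply is that an unadjusted difference with Fisher's test is a legitimate analysis of a secondary binary endpoint, and that the protocol uses it consistently for its binary efficacy items ((3), (8), (9) and (13)). The same recovery rate already receives adjusted analyses at 1 and 2 years in 10.5.2. This stands: nothing in item (3) biases the estimate, and more powerful analyses of these data are planned.

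It also stands that the covariate gain is assumed. The protocol gives no prognostic strength. The recovery rate is already scaled by 17 minus the preoperative score, so what preoperative JOA still adds is unknown. If the factors explain nothing, the gain is nil.

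A reader might infer that power is thrown away for nothing. That goes too far. Fisher guarantees a size of at most 5%, while Pearson ran at 5.6% and a standardised logistic analysis with delta-method errors at 5.4 to 5.9% under no difference. A linear adjustment with HC3 robust errors ran at 4.8 to 5.2%. Part of the apparent loss is the price of guaranteed error control.

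A reader might also infer that the trial's main conclusion is at risk. The documents do not support that. Success is judged only on the adjusted mean difference against −20%, and the 16-point deficit used here lies inside that margin. A non-significant Fisher result would not show non-inferiority at any power.

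Finally, 10 and 10.5 leave details to a separate analysis plan, which could add an adjusted analysis. But the protocol itself names the test and the interval in item (3), and the interval named cannot do what is asked. None of these replies removes that fault.

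**Conclusion.** The point holds as an efficiency and specification matter of low severity. Item (3) is valid but conservative, and its interval method does not match its estimate.

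About 6 points of power are lost to Fisher. That figure needs only the two responder proportions. About 0 to 8 further points are lost to the omitted covariates, depending on an R² the protocol does not state. The interval would narrow by at most about 1 point, so precision is not the main argument for adjusting; consistency with the primary analysis and a properly defined interval are. Normality serves mainly to translate mean deficits into responder proportions, and the true recovery rate cannot exceed 100%. The simulations carry an error of about 1 point, and those behind the 10- and 20-point rows used simple randomisation rather than minimisation.

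**What to change.** Reword 10.5.3 item (3) for both 1 and 2 years. Make the main result a standardised (marginal) risk difference from a logistic model with arm, preoperative JOA score, age group, sex, diagnosis and facility. Facility is a minimisation factor that 10.5.2 does not include. Give the risk difference a robust 95% confidence interval in place of Clopper-Pearson. Keep Fisher's test as supportive, or as the fallback when data are sparse.

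State that the interval is the result to be read, since no responder margin is set and a non-significant difference is not evidence of non-inferiority. If the sponsor prefers to stay unadjusted, the minimum repair is a Newcombe or Miettinen-Nurminen interval for the difference.

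The cost is analysis wording only: no new data, visits or patients. The small downside is that the adjusted test holds its size only approximately, whereas Fisher's is guaranteed.

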(4) ～(6)　The JOA score is a physician-led assessment of spinal cord symptoms originating from the cervical spine. Patient-reported outcomes such as EQ-5D, VAS, and NDI were set as secondary endpoints. Furthermore, EQ-5D will also be used as the utility value when calculating the incremental cost-effectiveness ratio.

(7) For safety assessment, the retention rate^7)^ (Figure 4), an objective indicator for enlarged lamina reclosure, was set as a secondary endpoint.

[figure not shown]

(8) As a safety endpoint, the proportion of hinge fractures in enlarged laminar segments on CT^8)^ was set as a secondary endpoint.

(9) As an endpoint for surgical goal achievement, the proportion of hinge fractures showing bone union on CT was set as a secondary endpoint.

(10) Postoperative cervical kyphotic deformity is a morphological change that leads to recurrence of spinal cord symptoms and poor outcomes in cervical laminoplasty^7-9)^. As indicators of kyphotic deformity, the C2-7 lordotic angle and C-SVA were set as secondary endpoints, along with the C7 slope as a factor influencing these (Figure 5).

[figure not shown]

(11) Reduction in the cross-sectional area of the paraspinal muscles (Fig. 6), which are cervical extensors, has been reported as a factor influencing occipital pain^20)^ and as a factor involved in post-laminoplasty reclosure^7)^. Therefore, the postoperative paraspinal muscle area at the C4-5 level was set as a secondary endpoint.

[figure not shown]

(12)(13) Post-laminectomy membrane, caused by posterior dural scarring after laminectomy, is considered a factor in spinal cord re-compression^21)^. However, its incidence rate across different laminoplasty techniques remains unclear. Postoperative dural canal area and the Grading of the mass posterior to the dural sac ^22)^ (Figure 7) were set as secondary endpoints to evaluate spinal cord re-compression.

[figure not shown]

(14) A key objective of this study is to demonstrate that the experimental treatment (suture- anchor) is non-inferior in efficacy and safety to the control treatment (mini-plate), while being less expensive and offering superior cost-effectiveness. As an indicator for comparing the cost-effectiveness between the experimental and control groups, the commonly used measure, ICER, was set as a secondary endpoint.

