The retention rate is calculated for each enlarged lamina identified on CT scans at postoperative 1 and 2 years, following previous reports^7)^ (Figure 4). The mean retention rate is also calculated for each patient.

(8) Proportion of hinge fractures at postoperative 1 and 2 years

(9) Percentage of bone union of gutter at postoperative 1 and 2 years

[Definition]

Using CT images at 1 and 2 years postoperatively, evaluate the presence or absence of hinge fractures (fractures of the groove created in the medial facet joint) and bone union in each enlarged lamina, following previous reports^8)^. Evaluate both on horizontal slices. A fracture is defined as a complete disruption of the cortical bone continuity of the target lamina. and bone union is defined as the formation of even partial bony continuity within the excavated groove region of the target lamina. The level and lateral side of each lamina are recorded.

[figure not shown]
(10) Sagittal alignment of cervical spine at postoperative 1 and 2 years (C-SVA, C2-7 angle, T1 slope)

[Definition]

Cervical spine alignment (C-SVA, C2-7 angle, C7 slope) is measured from plain radiographs at postoperative 1 and 2 years, according to previous reports^7)^ (Figure 5). Note that the C2-7 angle is denoted with a positive (+) sign for lordosis.

(11) Paraspinal muscle cross-sectional area (C4/5 level) at postoperative 1 and 2 years

[figure not shown]
[Definition]

Measure the cross-sectional area of paraspinal muscles (mm^2^) on the C4/5 slice of T2-weighted images according to a previous report^20)^, and calculate the total values for each side (Figure 6).

(a: multifidus, b: cervical semispinalis, c: cervical splenius capitis, d: splenius capitis)

(12) Dural sac cross-sectional area (C3/4, C4/5, C5/6, C6/7 levels) at postoperative 1 and 2 years

[Definition]

Measure the dural canal cross-sectional area (mm^2^) on the T2-weighted horizontal slice at each of the C3/4, C4/5, C5/6, and C6/7 levels, following the method described in a previous report^21)^ (Figure 7).

(13) Grading of the mass posterior to the dural sac at postoperative 1 and 2 years

［Definition］

The classification of posterior dural canal compression on the central slice of the T2 sagittal image is evaluated according to a previous report^22)^ (Figure 7).

[figure not shown]

(14) Incremental Cost-Effectiveness Ratio (ICER)

[Definition]

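### Clopper-Pearson, a one-sample method, is prescribed for the confidence interval of a between-group difference in proportions in Section 10.5.3 items (3), (8), (9) and (13)

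*Protocol*

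**What the plan says.** Section 10.5.3 treats four binary secondary endpoints alike.

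- Item (3), MCID achievement: "calculate the difference in the proportion achieving the MCID (52.8% recovery rate) and its 95% confidence interval, then perform Fisher's exact test".
- Items (8) and (9), hinge fracture and gutter bone union: "calculate the difference in the percentage for each evaluation item and its 95% confidence interval, and perform Fisher's exact test".
- Item (13), severe posterior compression: "calculate the difference in the proportion for each evaluation item and its 95% confidence interval, then perform Fisher's exact test".

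Each block ends with the same instruction: "Use the Clopper-Pearson method to calculate the confidence interval". Per-group proportions are to be calculated, but no interval is requested for them. The difference is the only quantity in these items that has one.

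On the unit of observation, Section 8.2 scores hinge fracture "and bone union in each enlarged lamina, following previous reports" and adds: "The level and lateral side of each lamina are recorded". The Section 5.1 rationale for item (8) describes "the proportion of hinge fractures in enlarged laminar segments on CT". Section 7.1.3 has 2 to 4 laminae expanded per patient. Section 10.5.3 items (8) and (9) give no denominator.

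**The concern.** The method named does not produce the quantity requested. Clopper-Pearson inverts the binomial test for one proportion, and no version of it exists for a difference of two. Whoever runs the analysis must either depart from the text or improvise. An obvious improvisation, combining the two single-arm intervals, is far too wide for a 95% interval and could hide a real difference.

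This matters most for hinge fracture. Section 5.1 calls it a safety endpoint, and Section 4 aims to show that the suture anchor is not inferior in efficacy or safety. Surgical complications, item (15), receive only counts and rates by group, so the hinge-fracture difference is one of the few comparative safety estimates in the plan.

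The second, conditional issue is the unit of analysis for items (8) and (9). Several laminae, each with two sides, come from one patient. If Fisher's exact test were applied to laminae or hinges, it would ignore the correlation within a patient.

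**Working it through.** **Inputs from the protocol.** Section 10.2 gives 172 evaluable patients, or 86 per arm; a control mean recovery rate of 50% with SD 40%; margin 20%; one-sided alpha 0.025; power 0.9; and about 20% dropout. The MCID threshold is 52.8%. Laminae per patient: 2 to 4.

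**The plan's own figure.** The protocol states no numerical interval for these endpoints; its only computed figures are the sample sizes. A noncentral-t calculation (difference 0, SD 40, margin 20) gives 86 per arm with power 0.903, or 172 in total. Then 172/0.8 = 215, which is 216 for equal arms. Both figures reproduce, and nothing below changes them.

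**Illustrative counts (assumed).** If recovery rates were normal with mean 50 and SD 40, the share above 52.8 would be Φ((50 − 52.8)/40) = Φ(−0.07) = 0.472. That is 0.472 × 86 = 40.6, say 41/86 in each arm. For a rarer outcome take 9/86 (about 10%) in each arm.

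**Route A: subtract single-arm Clopper-Pearson limits.** For x events in n, the limits are the 2.5% quantile of Beta(x, n−x+1) and the 97.5% quantile of Beta(x+1, n−x). The difference interval is then (L1 − U2, U1 − L2).

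- 41/86: limits 36.8% and 58.7%, giving ±21.9 points.
- 9/86: limits 4.9% and 18.9%, giving ±14.0 points.

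**Route B: Newcombe interval.** Take Wilson limits (l, u) for each arm. With equal observed proportions p, the half-width is √[(p − l)² + (u − p)²].

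- 41/86: p = 0.477, Wilson limits 0.374 and 0.581; √(0.102² + 0.104²) = 0.146, giving ±14.6 points.
- 9/86: p = 0.105, Wilson limits 0.056 and 0.187; √(0.049² + 0.082²) = 0.096, giving ±9.6 points.

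**Coverage**, by exact binomial enumeration at 86 per arm with equal true proportions:

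| True proportion | Route A | Newcombe |
|---|---|---|
| 47% | 99.7% | 94.4% |
| 10% | 99.7% | 95.9% |

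Route A is 21.9/14.6 = 1.5 times as wide as needed at 41/86.

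**Conditional check: unit of analysis for (8) and (9).** Assumptions not in the protocol: intraclass correlation (ICC) 0, 0.1 or 0.3; event rate 10% or 50%; 3 laminae, or 6 hinges (3 laminae × 2 sides), per patient. The design effect is 1 + (m − 1) × ICC. Beta-binomial data were simulated under no group difference (3,000 runs, 86 per arm), with Fisher's exact test at two-sided 5%. Ranges are over the two event rates.

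| Units per patient | ICC | Design effect | Type I error, unit = lamina or hinge |
|---|---|---|---|
| 3 | 0 | 1.0 | 2.9-3.5% |
| 3 | 0.1 | 1.2 | 6.2-6.3% |
| 3 | 0.3 | 1.6 | 9.2-10.2% |
| 6 | 0 | 1.0 | 4.0-4.6% |
| 6 | 0.1 | 1.5 | 8.7-9.8% |
| 6 | 0.3 | 2.5 | 19.2-20.3% |

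Fisher's test on patients (at least one event) stayed at or below 3.8% in all of these scenarios.

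**The case against.** Subtracting limits is a procedure the protocol never prescribes. It is conservative, and a competent analyst would probably substitute a standard two-sample interval in the SAP, which Section 10 allows to alter methods. This stands as a limit on the size of the problem: ±21.9 illustrates one improvisation and is not the plan's stated interval. It does not rescue the sentence. The protocol names a specific method for a specific quantity, and the two do not fit. A per-arm reading does not work either, because no per-arm interval is requested.

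A reader might go further and infer that the plan tests laminae or hinges as independent units, so that its p-values are wrong. The document does not support that. Section 10.5.3 gives no denominator. The full analysis set is a set of cases, so a per-patient percentage is a natural reading, and per-lamina recording would be needed to derive any-fracture-per-patient as well. The Section 5.1 rationale points towards segments for (8), but for (9) it describes yet another denominator, the share of hinge fractures showing union. A per-patient summary is given for retention rate, item (7), and none for the hinge outcomes. The fair conclusion is that the unit is left open. Items (3) and (13) give one outcome per patient per visit, so clustering cannot affect their Fisher p-values.

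**Conclusion.** The instruction is wrong as written for items (3), (8), (9) and (13): a one-sample method is assigned to a two-sample quantity, so the interval is undefined. That conclusion needs no assumption. The size does: if the arms' limits were subtracted, the interval would be about 1.5 times too wide at 41/86 per arm, with 99.7% coverage.

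The unit-of-analysis point is conditional. Inflation of type I error to about 6-10% (3 laminae) or 9-20% (6 hinges) requires the lamina or hinge to be the unit and an ICC of 0.1 to 0.3, neither of which the protocol states. Fisher's test at patient level is sound.

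Severity is minor. These are secondary endpoints with no margin or decision rule attached. The primary covariance analysis, its −20% criterion and the sample size of 172/216 are untouched.

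**What to change.** In Section 10.5.3, replace the Clopper-Pearson sentence in items (3), (8), (9) and (13) with a named two-sample interval for the difference, Newcombe or Miettinen-Nurminen. If single-arm intervals are wanted, say so and keep Clopper-Pearson for those only.

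For items (8) and (9), state the unit of analysis. Either define a patient-level outcome and keep Fisher's exact test, or report lamina-level rates with a GEE model clustered by patient.

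The cost is about two sentences in the protocol, mirrored in the SAP, using standard software. No extra data are needed, since level and side are already recorded. The change should be made before the data are analysed.
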